## Sampzle size

Assuming a standard deviation of LOS, excluding outliers, of 4.5 days, which is assumed to be equivalent across the two periods defined by the application of the protocol (pre and post), the estimated sample of approximately 300 patients provides more than 80 % power to show a mean reduction in the LOS of 2 days, from 10 to 8 days, with a one-sided alpha error of 5 %. This calculation incorporates the clustering of observations within the same center, assuming an intra-cluster correlation coefficient of less than 7 % (rho=0.07).

## Statistical analysis

Outcomes of continuous nature will be described using mean value and standard deviation, or median and interquartile range, as appropriate. The occurrence of outcomes of dichotomous nature will be described using absolute frequencies and percentages. To account for the clustering of patients within the same center, comparisons of outcomes between the two periods of ERAS protocol implementation will be conducted using generalized linear mixed-effects models. The functional link and the distribution family will be defined based on the distribution of the outcome variable of interest. Comparisons will be adjusted in the models for the peritoneal cancer index (PCI), the surgical complexity (with or without HIPEC), and for any patient potentially unbalanced prognostic factors in the distribution of the two periods.

The coefficient for the effect of the protocol on the mean LOS (primary endpoint) will be presented together with a one-sided 95 % confidence interval (CI), in accordance with the sample size assessment based on the one-tailed test. For coefficients pertaining to secondary endpoints, 95 % confidence intervals (CIs) will be presented on both sides. Exploratory subgroup analyses will be conducted according to peritoneal cancer index (PCI) and surgical complexity (CRS ± HIPEC).

Within the case report form, required fields with mandatory completion have been identified to investigate the application of various pre-, intra-, and post-operative ERAS items. Adherence to these items will be quantified as a percentage, and its impact on key outcomes (length of hospital stay, complications, readmissions, and bowel motility recovery) will be evaluated through a sensitivity analysis using mixed effects models, with adjustments for adherence level.

Additional sensitivity analyses will be performed by imputing missing data using multiple imputation techniques.

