**Methods:**

The EPICH study is a multicenter, prospective, interventional trial conducted across 20 centers in Italy. A total of 300 patients undergoing CRS±HIPEC will be enrolled in two sequential phases: standard perioperative care followed by ERAS protocol implementation. The primary endpoint is the mean hospital length of stay (LOS). Secondary endpoints include postoperative complications, ICU admission, readmission rates, bowel function recovery, mortality, and patient-reported quality of recovery. The ERAS protocol includes prehabilitation, anemia and nutritional optimization, intraoperative fluid and pain management, and early mobilization and oral feeding. Data will be analyzed using random-effects linear models to account for center-level variation and confounding factors.

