## Patients and methods

### Study design

EPICH study is a multicenter, prospective, interventional, cohort study with a pre-post design assessing the perioperative management according to the ERAS protocol in patients with peritoneal metastasis undergoing cytoreductive surgery with or without HIPEC.

Approximately 300 patients will be enrolled in 20 centers over 12 months. In the first period (approximately 4 months, 100 patients planned) the usual perioperative procedures will be described. In the second phase (approximately 8 months, 200 patients expected), the participating centers will apply the defined and agreed ERAS protocol.

The following elements of the ERAS protocol will be monitored during the study: prehabilitation and preoperative counselling, dietary assessment and possible nutritional support, antibiotic prophylaxis and bowel preparation, preoperative fasting management and postoperative resumption of fluid/solid intake per os, management of infusions and intra/postoperative analgesic therapy.

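### The random-centre model lets some between-centre difference into the ERAS effect on length of stay if centres differ in their ERAS share and that share is related to their usual stay; estimating the effect within centres is a cheap safeguard

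*Protocol article*

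**What the plan says.** The abstract of the protocol article states: "Data will be analyzed using random-effects linear models to account for center-level variation and confounding factors". The Statistical analysis section repeats the choice for all outcomes: "comparisons of outcomes between the two periods of ERAS protocol implementation will be conducted using generalized linear mixed-effects models". The listed adjustment covers the peritoneal cancer index, HIPEC or not, and patient prognostic factors found unbalanced between periods. All of these are patient-level terms. No fixed centre effect is named, nor any term that separates within-centre from between-centre differences.

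The Study design section fixes the layout: "Approximately 300 patients will be enrolled in 20 centers over 12 months". It goes on: "In the first period (approximately 4 months, 100 patients planned) the usual perioperative procedures will be described". About 200 patients are then expected over about 8 months, in which "the participating centers will apply the defined and agreed ERAS protocol". The totals of 100 and 200 are study-wide, and no split per centre is given.

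**The concern.** A random intercept accounts for correlation between patients of one centre. It does not by itself remove confounding by centre. The estimated period effect is a weighted average of two contrasts. One is the before-after change inside each centre. The other compares centres that have many ERAS patients with centres that have few. The second is valid only if a centre's underlying LOS is unrelated to its ERAS share.

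Period is set by calendar time, not by randomisation. A centre that opened late or recruited slowly at first would contribute mostly ERAS patients. If such centres also discharge earlier as a habit, that habit would count partly as an ERAS benefit in a one-sided test at 5%. If they discharge later, a real benefit would be diluted. Adjustment for case mix would not remove a difference in discharge practice.

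**Working it through.** **Inputs from the article.** 20 centres; about 100 usual-care and 200 ERAS patients (Study design). "Assuming a standard deviation of LOS, excluding outliers, of 4.5 days", ICC 0.07, target reduction 2 days, one-sided 5% (sample size section).

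**The plan's own figure.** Average centre size is 300/20 = 15, so the design effect is 1 + 14 × 0.07 = 1.98. SE = 4.5 × √(1.98 × (1/100 + 1/200)) = 0.776. Power = Φ(2/0.776 − 1.645) = 82.5%. The claim of more than 80% is reproduced and is not in question.

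**Variance components.** Between centres: 0.07 × 20.25 = 1.42, SD 1.19 days. Within centres: 0.93 × 20.25 = 18.83, SD 4.34 days.

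**Formulas** (linear model, variance components taken as known, no covariates). Centre i has n_i patients, ERAS share p_i and centre effect u_i.
- Within-centre information: W = Σ n_i p_i (1 − p_i) / 18.83
- Centre weight: w_i = 1/(1.42 + 18.83/n_i), with p̄ the w-weighted mean share
- Between-centre information: B = Σ w_i (p_i − p̄)²
- Bias with a random intercept: Σ w_i (p_i − p̄) u_i / (W + B)
- SE with random centres: 1/√(W + B); with fixed centres: 1/√W
- One-sided error: Φ(−bias/SE − 1.645)

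**Worked example.** Four centres have 10 ERAS patients only; the other 16 have 6 usual-care and 10 ERAS patients. W = 16 × 3.75/18.83 = 3.186. The weights are 0.303 and 0.385, so p̄ = 0.687 and B = 0.142. If the four centres have stays 1.19 days shorter, the bias is 4 × 0.303 × 0.313 × (−1.19)/3.328 = −0.14 days. SE = 0.548 and the error is Φ(0.136/0.548 − 1.645) = 8.1%. With fixed centres, SE = 0.560.

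**Scenarios.** The splits, gaps and correlations are assumptions. In the ERAS-only rows every centre has 10 ERAS patients, and the remaining centres share about 100 usual-care patients.

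| Assumed scenario | Weight of between-centre part | Bias (days) | One-sided error | SE random / fixed |
|---|---|---|---|---|
| Equal 5/10 in all centres | 0% | 0 | 5% | 0.531 / 0.531 |
| 1 ERAS-only centre, 1 SD shorter | 1.0% | −0.03 | 5.7% | 0.534 / 0.536 |
| 2 ERAS-only, 1 SD | 2.0% | −0.07 | 6.5% | 0.536 / 0.541 |
| 4 ERAS-only, 1 SD | 4.3% | −0.14 | 8.1% | 0.548 / 0.560 |
| 4 ERAS-only, 2 SD | 4.3% | −0.27 | 12.5% | 0.548 / 0.560 |
| 6 ERAS-only, 1 SD | 7.0% | −0.20 | 10.1% | 0.551 / 0.572 |
| 6 ERAS-only, 2 SD | 7.0% | −0.41 | 18.3% | 0.551 / 0.572 |
| 2 to 8 usual-care of 15, correlation −0.5 | 6.3% | −0.23 | 10.8% | 0.550 / 0.569 |
| 0 to 10 usual-care of 15, correlation −0.5 | 15.1% | −0.36 | 15.5% | 0.575 / 0.624 |

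**Limits.** If centre LOS is unrelated to ERAS share, the expected bias is zero in every row. If the ERAS-only centres have 15 patients each instead of 10, six of them at 2 SD reach −0.57 days and 26%. A perfect correlation in the widest split reaches −0.73 days. These are bounds, not expectations.

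**The case against.** Three points on the other side stand.

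- **Two conditions are needed.** A reader might infer that unequal ERAS shares alone bias the result. They do not: without an association between share and centre LOS, the between-centre part is legitimate information. The article reports no such association.
- **The design limits the problem.** A reader might also infer that nothing restrains the imbalance. The article describes two sequential phases run by the participating centres over about 4 and 8 months. On that plan each centre contributes to both phases at roughly 1:2, where the leak is near zero. No ERAS-only centre is described. Chance variation in shares alone gives the between-centre part only about 3% of the weight.
- **The upper scenarios are close to the extreme.** A gap of 2 SD for 4 of 20 centres uses 0.2 × 0.8 × 4 = 64% of the between-centre variance, a correlation of 0.80. For 6 of 20 it uses 84%, a correlation of 0.92.

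The random intercept also already helps. If five centres with stays 2 days shorter join only in the ERAS phase, the bias is −0.39 days, against −0.75 with no centre term. In the diluting direction little is lost: with +0.27 days and SE 0.548, power for 2 days is Φ((2 − 0.27)/0.548 − 1.645) = 93%.

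It can be said that mixed models are standard here and that the exact specification belongs in an analysis plan that is not shown. That is fair as to detail, and a within-between term would be compatible with the stated model. But the article does state random centre effects and a list of patient-level covariates, and as stated this does not isolate the within-centre change.

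**Conclusion.** The point holds in a conditional and modest form. The stated model uses some between-centre information once ERAS shares differ. The primary coefficient is biased if centre LOS is also related to those shares, which a non-randomised period does not rule out. The direction is unknown.

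Under the intended schedule the expected size is small: −0.03 to −0.07 days and about 6% one-sided error with one or two ERAS-only centres at 1 SD. About −0.3 to −0.4 days and 12% to 18% require large departures from the schedule, a strong association, or both. A reader might conclude that centre mix could produce the planned 2-day reduction on its own. The figures do not support that: −0.41 days is about one fifth of it, and even the −0.73-day bound is well short.

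The sizes rest on the plan's SD and ICC, a linear model without covariates, and assumed per-centre splits. This is a cheap improvement to the analysis, not an error that invalidates the trial.

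**What to change.** In the primary LOS model, estimate the ERAS effect within centres by one of two routes:
- fit centre as a fixed effect (20 levels); or
- keep the random intercept and add each centre's proportion of ERAS-period patients, computed in the analysed set, as a covariate.

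The ERAS coefficient then reflects the before-after change inside centres, which is the comparison a pre-post design is meant to give. Under the second route this is exact only without other covariates, or if their centre means are added too. A random centre-by-period term can still be included. State that centres with patients in one period only add nothing to this contrast.

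**Cost.** A change of analysis wording, with no extra patients or data. The SE is unchanged with equal splits (0.531), about 2% to 4% larger with four to six ERAS-only centres, and about 8.5% larger in the widest split tried (0.624 against 0.575). Power for 2 days with fixed centres is about 98% with equal splits and 94% in that widest split, still above the planned 80%. The change does not deal with time trends inside centres, which are a separate matter.

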## Ethics and data collection

The study will be conducted in accordance with the ethical principles set out in the Declaration of Helsinki and the standards of Good Clinical Practice, ensuring compliance with regulatory requirements for participant data protection. Prior to enrollment, participants will be provided with comprehensive information about the study, both verbally and in the form of a detailed written consent document. Ethical approval for the study was granted by the Ethical Committee “CET Interaziendale Città della Salute e della Scienza di Torino” on 20/11/2024.

The Case Report Form (CRF) is accessible within a dedicated section of the EPICLIN electronic platform (https://new.epiclin.it/it/eras_carcinosi/). EPICLIN, developed and managed by the Clinical Epidemiology Unit, AOU Città della Salute e della Scienza di Torino complies with all security requirements outlined in the General Data Protection Regulation (EU Regulation 2016/679).

For each participant, an individual identifier (ID) will be generated at the respective recruitment center. A first database will store the association between the participant’s personal data and their ID, ensuring the separation and confidentiality of sensitive information. A second database, hosted on the EPICLIN platform, will contain the ID and the clinical data collected for the purposes of the study, without including any personal information about the participant.

The recruitment officer at each center will be responsible for entering the clinical data into the second database. The system utilized is a validated and secure database, fully compliant with current data protection regulations.

## Discussion

The implementation of the ERAS (Enhanced Recovery After Surgery) protocol in the context of cytoreductive surgery (CRS) and hyperthermic intraperitoneal chemotherapy (HIPEC) represents a significant advancement in perioperative care for patients with peritoneal surface malignancies. The EPICH study builds upon the growing body of evidence supporting ERAS principles across various surgical specialties and extends it to a highly complex patient population with unique perioperative challenges.

CRS and HIPEC procedures are associated with substantial physiological stress, high postoperative morbidity, and prolonged recovery periods due to their extensive nature and the immunosuppressive effects of intraperitoneal chemotherapy [21], 22]. In this study, the ERAS approach seeks to mitigate these challenges by integrating multimodal strategies such as prehabilitation, optimized nutritional support, enhanced anesthesia protocols, and early postoperative mobilization.

Existing literature has demonstrated that ERAS protocols improve outcomes by reducing postoperative complications and hospital stays while enhancing patient satisfaction [23]. For example, patients undergoing elective colorectal or gynecological surgeries under ERAS protocols have shown a mean reduction in length of stay by approximately 2 days and fewer postoperative complications compared to conventional care​ [2]. The primary endpoint of the EPICH study aligns with these findings, aiming to confirm similar benefits in patients with peritoneal malignancies.

Despite its potential benefits, the adoption of ERAS in CRS ± HIPEC has faced barriers, including the complexity of the protocol, interdepartmental coordination, and the need for high adherence to multifaceted guidelines. Surveys conducted as part of the EPICH study revealed these challenges, particularly related to the large number of protocol items and the variability in institutional resources [20]. Addressing these issues, the study employed a consensus-based selection of ERAS elements to ensure practicality and efficacy in this specific surgical context.

The EPICH study design, comparing standard perioperative care with ERAS-based management, offers a pragmatic approach to evaluating the protocol’s impact. By focusing on high-consensus items such as prehabilitation, multimodal analgesia, GDFT, early mobilization and feeding, if possible, the study aims to address logistical constraints while preserving core ERAS principles.

Preliminary data from ERAS applications in CRS ± HIPEC suggest promising results. Studies have shown improved bowel function recovery, fewer ICU admissions, and reduced hospital costs without compromising patient safety [19]. Additionally, the integration of preoperative measures such as anemia correction and nutritional optimization aligns with broader evidence linking these interventions to better surgical outcomes.

By incorporating these strategies, the EPICH study is poised to provide robust data supporting the adaptation of ERAS protocols to the complex CRS ± HIPEC setting. If successful, the findings could promote wider adoption and ultimately improve the quality of care for patients with peritoneal metastasis.

While the study design is robust, certain limitations must be acknowledged. The reliance on a multicenter approach introduces potential variability in protocol adherence, which could impact outcomes. Future research should explore the long-term effects of ERAS on patient-reported outcomes, cost-effectiveness, and the potential for further streamlining protocol components.
